## Abstract

**Background:**

Protection and promotion of sexual health is of great importance for educable intellectually disabled adolescent girls; since they are prone to high risk sexual vulnerabilities and consequences, such as unwanted pregnancy, sexually transmitted infections, and acquired immune deficiency syndrome. Although the rights of intellectually disabled adolescents have been emphasized through the recent years, their sexual health care is still a challenge for parents, teachers, caregivers, and service providers. This study aims to present a comprehensive sexual health care program for educable intellectually disabled adolescent girls.

**Methods:**

This study is carried out by an exploratory sequential mixed qualitative-quantitative methods approach including three sequential phases. The researcher represents sexual health state of educable intellectually disabled adolescent girls using a qualitative approach. In the onset of the second phase, a comprehensive sexual health care program is designed for educable intellectually disabled adolescent girls. In this regard, in addition to qualitative studies, some related papers and texts are used. The suggested program of expert panel is approved based on prioritization guidelines. Then, in the third phase and after different stages of finalization of the program, its affectability is evaluated regarding improvement of sexual health state of educable intellectually disabled adolescent girls.

**Discussion:**

It is expected that from the results of the present mixed methods study, by presenting a comprehensive sexual health program for educable intellectually disabled adolescent girls, lead to improvements in the sexual health of these girls. Moreover, it wants to reduce risky sexual behaviors, sexual abuse and harassment, and their consequences in adolescent girls in order to improve sexual health state of the society. If this program works, it can become one of the leading education and care guidelines for sexual health care of intellectually disabled adolescent girls.

**Trial registration:**

IRCT20160224026756N5. Registered 22 June 2018.

## Plain English summary

Intellectually disabled adolescents, as well as normal people, experience different changes, such as secondary sexual characteristics and sexual desires. However, these changes may expose them to more problems and challenges due to their low intelligence quotient (IQ). Their poor understanding of inappropriate behaviors, inability in differentiating between malicious and normal sexual relations, problems in establishing negotiating relationships, and problem with reporting sexual abuses are some of the examples of their sexual vulnerabilities. These sexual harassments may be followed by unwanted pregnancies, sexually transmitted infections (STIs), human immunodeficiency virus and acquired immune deficiency syndrome (HIV/AIDS). Frequencies of these sexual abuses ultimately cause depression and anxiety in the adolescents. The findings of this study are suitable sources for selecting the best intervention of sexual health care of educable intellectually disabled adolescent girls. This study is carried out by an exploratory sequential mixed qualitative-quantitative methods approach including three sequential phases.

In this study, the researcher represents sexual health state of educable intellectually disabled adolescent girls using a qualitative approach. In the onset of the second phase, a comprehensive sexual health care program is designed for educable intellectually disabled adolescent girls. In addition to qualitative studies, some related papers and texts are studied. The suggested program of expert panel is approved and validated based on prioritization guidelines. In the third phase and after different stages of finalization of the program, its affectability is evaluated regarding improvement of sexual health state of educable intellectually disabled adolescent girls. It is expected that from the results of the present mixed methods study, by presenting a comprehensive sexual health program for educable intellectually disabled adolescent girls, lead to improvements in the sexual health of these girls. Moreover, it wants to reduce risky sexual behaviors, sexual abuse and harassment, and their consequences in adolescent girls in order to improve sexual health of the society.

It should be noted that intellectually disabled adolescents, as well as normal people, experience different changes which occur in this age, such as secondary sexual characteristics and sexual desires [16–20]. However, these changes may expose them to more problems and challenges due to their low IQ [21, 22]. According to study findings, a wide range of sexual problems and manifestations can be observed in intellectually disabled adolescents, such as voyeurism, masturbation, divulging sexual desires in the public, expressing a desire to have sexual relationships with others and even with close ones, sexual abuse, poor understanding of inappropriate behaviors, inability in differentiating between malicious and normal sexual relations, problems in establishing negotiating relationships, and problem with reporting sexual abuses [22–25]. According to the researches, social and cultural context is an obstacle for discovering sexual desires of intellectually disabled adolescents. Although the rights of intellectually disabled adolescents have been emphasized through the last 40 years, their sexual health care is still a challenge for parents, teachers, caregivers, and service providers [26–28].

Although a lot of studies have been done on sexual problems of intellectually disabled adolescents and children in different countries around the world, there is a scarcity of them in Iran, especially studies using quantitative methodology and questionnaires. Since quantitative approach is limited in explaining some of the phenomena, such as humanistic values, cultural values, and human relations, it should be mixed with a qualitative approach in order to for the researcher to be able to understand deep and internal realities of human beings [29]. Therefore, with regard to different social, cultural, and religious contexts of Iran in comparison with other countries, a mixed (qualitative-quantitative) methods approach is used for identifying sexual needs and problems of educable intellectually disabled adolescent girls in order to design and execute a comprehensive sexual health care program for them.

### Objectives

Objectives of each phase are as the following:

#### Objectives of the first phase: qualitative study

Explaining sexual health status of educable intellectually disabled adolescent girls.

#### Objectives of the second phase: program design

Designing a primary intervention program based on extracted data from qualitative phase and reviews.

#### Objectives of the third phase: quantitative study

Explaining affectability of the comprehensive sexual health care program for educable intellectually disabled adolescent girls.

## Methods/Design

This study is carried out using an exploratory sequential mixed qualitative-quantitative methods approach including three sequential phases. The researchers use a qualitative approach to explain sexual health status of educable intellectually disabled adolescent girls and the required strategies for their sexual health care. For this end, they analyze understandings and experiences of the participants. In this phase of the qualitative study, the data are collected via semi-structured individual in-depth interviews; focus group discussions, and field noting. The participants are selected with a purposeful approach and with maximum variety. Simultaneous with data collection, the interviews will be analyzed with a conventional qualitative content analysis method. Sampling will be continued until saturation occured. After saturation and at the end of interviews, the researcher enters the second phase of the study in which a comprehensive program will be designed for sexual health care of educable intellectually disabled adolescent girls. For this end, a literature review of papers and texts will be used in addition to the results of qualitative study. Then, the suggested program will be validated based on prioritization guidelines. In the third phase and after different stages of finalization of the program, its affectability is evaluated regarding improvement of sexual health state of educable intellectually disabled adolescent girls. The collected data will be processed by SPSS Version 17.0 software and will be analyzed with descriptive-analytic statistical methods (Fig. 1).

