#### Research sample

Study sample includes mothers of educable intellectually disabled adolescent girls who will be selected by convenience sampling and have all the inclusion criteria.

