#### Research variables

In this clinical trial, the designed interventions are considered to be independent variables, and awareness, attitude, and mothers’ self-efficacy in the field of sexual health care of educable intellectually disabled adolescent girls are considered to be dependent variables.

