#### Data collection methods

Questionnaires evaluating awareness and attitude, and mothers’ self-efficacy in the field of sexual health care of educable intellectually disabled adolescent girls are used in the quantitative phase of this trial. Researcher-made questionnaires are used for evaluation of mothers’ awareness and attitude. Reliability and validity of these questionnaires will be determined. Moreover, general self-efficacy questionnaire, introduced by Schwarzer & Jerusalem, is used for evaluation of mothers’ self-efficacy [32]. Mothers’ awareness questionnaire includes 23 questions with three options of “true, false, I do not know”. In measuring awareness score, one score will be given to the participants for each true answer. Minimum and maximum awareness scores are 0 and 23, respectively. Mothers’ attitude questionnaire includes 18 questions with a 5-point Likert scale of “strongly disagree, disagree, neither agree nor disagree, agree, and strongly agree”. Scoring is done from 0 to 4. Minimum and maximum attitude scores are 0 and 72, respectively. Self-efficacy questionnaire includes 10 questions with 4 options of “never true, rarely true, sometimes but infrequently true, and always true”. In measuring self-efficacy score, one score will be given to the participants for each true answer. Minimum and maximum self-efficacy scores are 0 and 10, respectively.

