#### The implementation method

The researcher will implement the designed program after obtaining permission from ethics committee of Isfahan University of Medical Sciences and the necessary coordination with authorities of The Ministry of Health and Welfare and The Ministry of Exceptional Education. This is done by referring to the centers covered by The Ministry of Health and Welfare and secondary exceptional schools and presenting a letter of introduction to the authorities of those centers regarding research objectives. After that, the researcher will be allowed to access to phone numbers of girls in secondary educational schools and centers covered by The Ministry of Health and Welfare, and call their mothers in order to explain research objectives and invite them to participate in the research. If the mothers are willing to cooperate, and have all the inclusion criteria, they will be selected by convenience sampling method with their informed consent. Mothers’ awareness, attitude, and self-efficacy will be considered as the suggested outcomes. Before intervention, the questionnaires will be filled by mothers in each of the three groups. Furthermore, the questionnaires will be refilled by mothers immediately and 1 month after the intervention.

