## Discussion

Multiple researches indicate that intellectually disabled adolescents need a comprehensive sexual health care program in order to be protected from sexual abuse and harassment and their adverse consequences, such as unwanted pregnancy, illegal abortions, STIs, and HIV/AIDS [33–39]. Negative attitudes of teachers and mentors toward sexual education of intellectually disabled adolescents, cultural obstacles, parent’s awareness and attitude, and sexual taboos have limited the design and implementation of such kind of comprehensive programs and have caused inattention to sexual health care of intellectually disabled adolescents [22, 40–42].

Moreover, the researchers have supported studies carried out on education interventions of parents of intellectually disabled adolescents as a sexual health care strategy which will reduce sexual abuse and harassment consequences [22, 43]. According to the importance of sexual health care of intellectually disabled adolescents, the present study aims to design and implement a comprehensive sexual health care program for these adolescents. The framework of this program will improve awareness, attitude, and self-efficacy of mothers in the field of sexual health care. So they can help their girls to have healthy relationships, protect themselves in unhealthy situations, and prepare themselves for a healthy, safe, and socially accepted sexual life. This mixed methods study and its resulted intervention program should be able to improve sexual status of these adolescent girls and reduce the consequences of sexual abuse and harassment, malicious sexual behaviors in them, and consequently, improve social health. If this program works, it can become one of the leading education and care guidelines for sexual health care of intellectually disabled adolescent girls.

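### The third phase is said to evaluate improvement in the girls' sexual health, but the trial enrols only mothers and measures only mothers' awareness, attitude and self-efficacy

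*Protocol article*

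**What the plan says.** Methods/Design describes the third phase as the stage at which the program is complete and "its affectability is evaluated regarding improvement of sexual health state of educable intellectually disabled adolescent girls". The same sentence stands in the Methods part of the Abstract and in the Plain English summary. It fixes what is to be evaluated (improvement in sexual health state) and in whom (the girls).

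The formal objective of the third phase is shorter: "Explaining affectability of the comprehensive sexual health care program for educable intellectually disabled adolescent girls". It names the girls as those the program is for, and gives no endpoint.

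The trial sections are about mothers throughout:

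- Research sample: "Study sample includes mothers of educable intellectually disabled adolescent girls who will be selected by convenience sampling".
- Research variables: awareness, attitude and "self-efficacy in the field of sexual health care of educable intellectually disabled adolescent girls are considered to be dependent variables". The awareness and attitude instruments under Data collection methods are explicitly mothers' questionnaires.
- The implementation method: mothers' awareness, "attitude, and self-efficacy will be considered as the suggested outcomes". After a baseline completion, "the questionnaires will be refilled by mothers immediately and 1 month after the intervention".
- Sample size: 27 per group, from differences of 2.9 (awareness), 11.3 (attitude) and 5 (mothers' self-efficacy).

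The Discussion, like the Discussion part of the Abstract, looks ahead to use of the program: "If this program works, it can become one of the leading education and care guidelines". Both also express the expectation that the girls' sexual health will improve and that abuse and harassment, or their consequences, will fall.

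**The concern.** The article fixes both sides of the comparison. It names an evaluation target in the girls, and it names the dependent variables, all in the mothers. A fuller protocol or analysis plan could refine how the mothers' scores are analysed, but it could not turn those scores into data on the girls. So this is not a matter of detail left to another document.

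What is at stake is the conclusion the trial may draw. The article makes guideline use conditional on the program working, without saying on which outcome that would be judged. With the evaluation sentence as it stands, a rise in mothers' questionnaire scores at 1 month could be reported as improved sexual health of a vulnerable group, although no information on that would have been collected.

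**Working it through.** The point rests on setting the statements side by side.

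| Element | Where | Concerns |
|---|---|---|
| Evaluation target | Abstract (Methods), Plain English summary, Methods/Design | Girls' sexual health state |
| Formal objective | Objectives of the third phase | Effect of the program; no endpoint named |
| Population and sample | Research population, Research sample | Mothers |
| Eligibility | Inclusion criteria | Parents' field of education; mothers' earlier training and literacy |
| Sample-size inputs | Sample size | Awareness, attitude, mothers' self-efficacy |
| Outcomes | Research variables, The implementation method | Mothers' awareness, attitude, self-efficacy |
| Instruments | Data collection methods | Questionnaires: awareness 0–23, attitude 0–72, self-efficacy 0–10 |
| Timing | The implementation method | Before, straight after, 1 month after |

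**Count of outcomes.** Three outcomes are listed. All three are questionnaires completed by mothers (3 of 3). None records a girl's knowledge, behavior, exposure to abuse, pregnancy or infection (0 of 3). The last assessment is at 1 month.

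**Distance of the self-efficacy measure.** Research variables describes self-efficacy specific to the girls' sexual health care, but the instrument named under Data collection methods is a "general self-efficacy questionnaire". This outcome is therefore further from the girls than its label suggests.

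**Could the first phase fill the gap?** It does address the girls' sexual health status, but it is qualitative and comes before the program is designed. It cannot show improvement under the program.

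**Does the sample size carry any girl-level quantity?** The stated figure is 27 per group, so 3 × 27 = 81 in all. No standard deviation is given, so 27 can be neither confirmed nor refuted. Working backwards for a two-group comparison, with two-sided 5% alpha (assumed) and 80% power:

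- 24 evaluable per group with 10% loss gives 24 / 0.9 = 26.7, rounded up to 27.
- The implied SD is d / [(1.960 + 0.842) × √(2/24)] = d / 0.809.
- That gives 2.9 / 0.809 = 3.59 (awareness), 11.3 / 0.809 = 13.97 (attitude) and 5 / 0.809 = 6.18 (self-efficacy).

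These SDs are assumptions and the point does not depend on them. The check shows only that every input is a mother-level score. No effect on the girls is specified, so power for the stated evaluation target cannot be derived.

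**The case against.** The best defence is that the trial specification is consistent. Population, sample size, variables, instruments and timing all concern mothers, and no planned calculation depends on the mismatched sentence. The Discussion also discloses the reasoning: the program is meant to raise mothers' awareness, attitude and self-efficacy so that they can help their daughters. On this view the outcomes are openly stated intermediate targets, and only a summary sentence is loosely worded.

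Much of that stands, and it rules out several stronger readings that a reader might infer:

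- *That the formal objective promises a girl-level endpoint.* It does not. It names the girls only as those the program is for. The explicit girl-level target is in the sentence that appears in the Abstract, the Plain English summary and Methods/Design.
- *That the article says the trial will demonstrate better sexual health or less abuse.* It does not. The relevant statements are hopes, expectations or conditionals.
- *That a 1-month follow-up is an error.* Nothing in the article promises longer measurement, so nothing is contradicted.
- *That a mothers-only trial is an invalid design.* It is a legitimate design for an aim stated in terms of mothers.

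What the defence does not remove is the sentence itself. In Methods/Design it is a statement of method, and it names a target on which no data will be collected. Disclosing a pathway is not the same as measuring it.

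**Conclusion.** The point holds as a contradiction between the stated evaluation target and the listed outcomes. It is not a failure of the design for a mothers-level question. The trial can address short-term change in three mother-reported scores. It cannot deliver an evaluation of improvement in the girls' sexual health state, because 0 of 3 outcomes concern the girls. The open wording of the formal objective leaves the mismatch unresolved.

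This rests on the text alone and on one assumption: that the outcomes named under Research variables and The implementation method are the complete set for the third phase. Those sections give no hint of others. The correction should be made, because it changes what may be concluded from a positive result.

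**What to change.** 1. In the Abstract (Methods), the Plain English summary and Methods/Design, say that the third phase evaluates the effect of the program on mothers' awareness, attitude and self-efficacy, straight after the intervention and at 1 month.
2. Add the same outcomes and times to the formal objective of the third phase.
3. In the Discussion and the Discussion part of the Abstract, tie the condition that the program works to those outcomes.
4. In the same two places, and where the Plain English summary repeats the expectation, mark improvement in the girls' sexual health and reduction in abuse and harassment as expected but not tested by this trial.

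The cost is wording and a more modest claim. Design, sample and follow-up are unchanged. Keeping the girl-level target would instead require an outcome about the girls, suitable follow-up and its own sample-size basis, which is a change of design and is not needed to resolve the contradiction.

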**Fig. 1 Fig1:**
[figure not shown]
Study visual diagram

### First phase: qualitative study

The first phase of this study is designed for answering the question of: “How is the sexual health status of educable intellectually disabled adolescent girls from the viewpoint of participants?”

This study will be carried out using a qualitative content analysis method.

#### Participants in the qualitative phase

Research community of the first phase consists of educable intellectually disabled adolescent girls, parents, teachers, mentors, psychologists, psychiatrists, consultants, gynecologists, midwives, and forensic medicine specialists. All of them have the experience of dealing with sexual problems of educable intellectually disabled adolescent girls.

#### Sampling method

In the present study, participants are selected with a purposeful sampling method and with maximum variety. They are selected based on maximum variety in age, education, social status, and job.

#### Inclusion criteria for participants

Tendency to participate in the study with informed consent for sharing information and participating in communication and interviews.Iranian citizenship and the ability to understand and speak in Farsi.No history of well-known psychiatric disorder.

#### Research environment

The participants are accessed through rehabilitation centers covered by the Ministry of Health and Welfare, exceptional education schools, consulting centers, hospitals, clinics, forensic medical centers, and psychiatrists’, gynecologists’, midwives’, and psychologists’ offices. The interviews will be done in the location and time selected by the participants for their ease and comfort.

